The most frequently reported disorders associated with war traumatization are posttraumatic stress disorder (PTSD) and major depression: studies reported prevalence rates of 33.5% for PTSD [7], and 29.5% for depression [8] among Syrian refugees. By contrast, in a representative study of the European general population that included six countries, the 12-month prevalence rates for PTSD and depression were 0.9 and 3.9%, respectively [9]. PTSD is often accompanied by comorbid physical complaints, of which chronic pain is most common. Among refugees with PTSD, prevalence rates of clinically relevant chronic pain ranged from 76% [10] to 88% [11].

Recent PTSD guidelines by the German Association of the Scientific Medical Societies (AWMF) indicate that a trauma adaptive psychotherapy should be provided for every patient diagnosed with PTSD [12]. During the first 15 months after arrival to Germany, however, psychosocial care for refugees cannot be fully ensured due to initially restricted access to the health care system, which is regulated through specific asylum law (Asylbewerberleistungsgesetz/AsylbLG). By contrast, refugees who have stayed in Germany for more than 15 months gain access to the statutory health insurance that covers psychotherapy. According to a verdict of the Federal Social Court, however, health insurance funds are not obliged to cover the costs for a qualified translator, if needed. Instead, regional/local social security offices make individual decisions whether translator expenses can be refunded. However, refunding cannot be guaranteed, and it can take an enormous amount of extra time until a decision is made [3]. Moreover, the number of specialized psychotherapists and translators is limited. It is thus difficult to provide treatment for PTSD to all refugees in need. Indeed, there is a clear lack of adequate health services in this regard. Likewise, research has shown that traumatized individuals perceive additional barriers (e.g. concerns related to stigma, shame and rejection), which may hinder them to seek for adequate treatment [13].

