### Expected benefits and harms

We expect that the low-threshold app-based intervention will lower posttraumatic symptom severity and associated secondary outcomes in favor of overall improved wellbeing and quality of life. Furthermore, since our self-help app will be in Arabic language, basal information regarding treatment options and disease management can be provided to a broad group of traumatized refugees without causing costs due to translation. This can help to compensate for the lack of adequate psychotherapeutic care for Syrian refugees in Germany. In case of an unexpected increase in symptom severity - the trauma-related content might initially trigger unpleasant memories and feelings - both study groups will be provided with contact information for professional help in case of emergency. Moreover, the occurrence of negative effects, regardless whether or not related to the trial, will be monitored.

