Healthcare resource use		x	only T2	yes
App usability (SUS)^a^		x	only T1	yes
User acceptance (TAM 3)^a^		x	only T1	yes

Note: ^a^to be assessed only in the intervention group

*DSI-SS* Depressive Symptomatology Index – Suicidality Scale [47], *PDS-5* Posttraumatic Diagnostic Scale for DSM-5 [30], *PHQ-9* Patient Health Questionnaire [31], *GAD* General Anxiety Disorder [48], *EQ-5D-5L* Euroqol Five Dimensions Questionnaire [49], *GSE* General Self-efficacy [50], *SSMIS-SF* Self-stigma of Mental Illness Scale – Short Form [51], *LSNS* Lubben Social Network Scale [52], *ESSI* Enriched Social Support Inventory [53], *PGI* Posttraumatic Growth Inventory [54], *RS-13* Resilience Scale [55], *Z-7* Zentralitätsskala [56], *SUS* System Usability Scale [36], *TAM-3* Technology Acceptance Model [37]

Ambiguous loss and prolonged grief - questions have been adapted from the German version of the Complicated Grief Inventory (ICG-D; [57]); Healthcare resource use – questionnaire was adapted from previous investigations and is available from the authors upon request [58]

We hypothesize that the app intervention reduces posttraumatic stress symptomatology (primary outcome), quantified using the Posttraumatic Diagnostic Scale for DSM-5 (PDS-5 [30]). The PDS-5 is a well-established self-report measure based on the diagnostic criteria of the DSM-5, which allows the assessment of posttraumatic stress symptom severity.

Regarding secondary outcomes, we moreover expect the intervention to reduce symptoms of depression, anxiety, and somatization. Positive intervention-related effects are also expected regarding quality of life, self-efficacy, perceived stigmatization, social support, ambiguous loss, and posttraumatic growth.

Use of resources in terms of health demands will be assessed using a cost book (bottom-up approach). Furthermore, we aim to gather information on user acceptance and usability of the self-help app using the System Usability Scale (SUS) [36] and Technology Acceptance Model (TAM3 [37]), respectively.

Last, meta-data stored in the app’s log-files will provide quantitative information about the use of the app, e.g. number of days used, number of worked-through modules, or operating time.

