**Fig. 3 Fig3:**
[figure not shown]
Schedule of enrollment, interventions and assessments. Completed SPIRIT 2013 figure of recommended content of enrolment, interventions, and assessments. Abbreviations: t1 = baseline; t2 = 4 weeks after baseline (post intervention); t3 = 16 weeks after baseline (follow-up). *assessed in intervention group only

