#### Statistical analysis

All acquired data will be examined with respect to potential inconsistencies and missing values, which will be replaced using multiple imputation methods [42], if appropriate. To detect potential systematic biases, a drop-out analysis will be performed. Internal consistencies of the newly translated inventories will be calculated to evaluate their reliability. All subsequent analyses will be treated as intention-to-treat or completer-analyses. Data-analysts will be blinded for group allocation.

Changes in primary and secondary outcomes will be described using mean scores and standard deviations, among others. Short and medium termed treatment effects will statistically be inferred by using linear mixed effect models accounting for relevant covariates. Usability as well as user acceptance of the app will be evaluated using descriptive statistics. The significance level of all analyses will be set to *p* < 0.05.

To assess the potential health economic benefits, we will perform analyses of the (i) actual costs and (ii) the ICER of the intervention. Costs will be quantified by the frequency of how often physicians and therapists are consulted (including days spent in a hospital) and valuated using current standard costs [43]. The app development expenses will be treated as economically reasonable overhead costs and added accordingly. To assess the interventions’ economic efficiency, the ICER will be calculated as the ratio between the difference of the actual costs and the difference of the averaged treatment effects (indexed by either quality-adjusted life years or primary outcome scores) between IG and CG. Respective confidence intervals will be derived by non-parametric bootstrapping. To visualize the ICERs statistical uncertainty, cost-effectiveness-acceptance curves will be constructed, indicating the probability of an acceptable ICER in relation to willingness to pay for an effect. Alternatively, net benefit regressions [44] can be applied to estimate the respective group specific net benefits while accounting for potentially confounding variables such as age, sex, and education.

The results of the study will be reported according to the guidelines of the Consolidated Standards of Reporting Trials (CONSORT) statement [45].

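### Service-use costs leave out newly started medication and interpreter-assisted contacts, and healthcare use is not asked at T1, so participants lost between T1 and T2 have no observed follow-up cost

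*Protocol article*

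**What the plan says.** All places are in the protocol article.

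- **Costed items (Statistical analysis).** "Costs will be quantified by the frequency of how often physicians and therapists are consulted (including days spent in a hospital", valued at current standard costs. The next sentence adds the intervention itself: "The app development expenses will be treated as economically reasonable overhead costs and added accordingly". The ICER is the arm difference in actual costs divided by the arm difference in mean effect, with effect measured as QALYs or as primary outcome scores.
- **Instrument (Outcomes).** "Use of resources in terms of health demands will be assessed using a cost book (bottom-up approach". The Table 1 note says that the "questionnaire was adapted from previous investigations and is available from the authors upon request". Its items and recall period are not shown.
- **Timing (Outcomes, Table 1; Fig. 3 legend).** The row "Healthcare resource use" is marked at baseline and, among the follow-ups, at T2 alone. PDS-5 and EQ-5D-5L are marked at baseline, T1 and T2. T1 is 4 weeks after baseline; for T2 the legend gives "t3 = 16 weeks after baseline (follow-up".
- **Translation.** Background reports that "health insurance funds are not obliged to cover the costs for a qualified translator, if needed", and that local social security offices decide on refunds case by case. Expected benefits and harms says that basic information in an Arabic app "can be provided to a broad group of traumatized refugees without causing costs due to translation".
- **Dropout (Sample size).** About 40%, with 234 at baseline to retain 140.

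**The concern.** Cost-effectiveness is a stated objective of the trial, so the rules for the ICER numerator deserve the same scrutiny as those for the effect. Two of the stated rules lose information.

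First, the list of costed services is short for this population. Interpreters are, on the protocol's own account, not reliably paid by the health insurer, so a standard unit cost per consultation need not contain them. Current psychopharmaceutical medication is an exclusion criterion, so any such medication used during follow-up was started after eligibility was established. That makes it a plausible consequence of what happens in the trial, and it is not costed.

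Second, the whole follow-up cost of each participant hangs on one visit, 16 weeks out, in a mobile population for which heavy loss is expected. Effects are observed at T1 and costs are not. A participant lost after T1 contributes effect data and no cost data, and a cost-effectiveness statement at T1, the time point on which the sample size rests, cannot be made from costs over the same period.

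**Working it through.** **1. The plan's own figure.** There is none for the cost endpoint. The dropout allowance is the only planning number that bears on this point, and it reproduces: 140 / (1 − 0.40) = 233.3, rounded up to 234; 234 − 140 = 94.

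**2. What enters the numerator.** Under the stated rule, the cost difference IG − CG per participant is

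ΔC = D_v × u + D_h × h + A

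where D_v and D_h are the arm differences in consultations and hospital days, u and h the standard unit costs, and A the app development cost per participant. With interpreters and medication included it becomes

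ΔC* = ΔC + D_i × c + D_m × m

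where D_i is the arm difference in interpreter-assisted contacts, c the interpreter cost per contact, D_m the arm difference in medication use and m its unit cost. With effect difference ΔE, the ICER moves by (D_i × c + D_m × m) / ΔE.

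- If D_i = D_m = 0, the omission has no effect.
- If the app group uses more of these items, its extra cost is understated.
- If it uses less, its saving is understated.

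The documents give no value for c, m, D_i or D_m. On direction they point both ways: Background says apps may make refugees readier to seek help (more contacts), while Expected benefits and harms says the app may partly make up for missing care (possibly fewer).

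**3. What the translation benefit refers to.** The benefit in Expected benefits and harms is delivery of information in Arabic. The Intervention section gives the control group the same psychoeducational information in an Arabic brochure. That saving therefore largely cancels in ΔC; only a difference in interpreter-assisted contacts would remain.

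**4. Timing.** Follow-up is 16 weeks, with T1 at week 4 and T2 twelve weeks later. Coverage by a single T2 questionnaire depends on its recall period, which is not shown, so these are assumed values:

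| Recall at T2 | Share of follow-up covered | Intervention month covered |
|---|---|---|
| 12 weeks | 12/16 = 75% | no |
| 16 weeks or more | 16/16 = 100% | yes |

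Asking at T1 (4 weeks back) and T2 (12 weeks back) covers 4 + 12 = 16 weeks, with no recall longer than 12 weeks.

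**5. A participant seen at T1 but lost before T2.**

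| Measure | Observed now | Observed if also asked at T1 |
|---|---|---|
| PDS-5 | T0, T1 | T0, T1 |
| EQ-5D-5L | T0, T1 | T0, T1 |
| Healthcare use | T0 only | T0, T1 |
| Follow-up weeks with observed cost | 0 of 16 | 4 of 16 (25%) |

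The Statistical analysis section allows multiple imputation. For this participant, follow-up cost could be imputed only from baseline cost and other variables.

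**6. How many such participants.** The 40% is not split by visit. If it is the total loss by T2, the number seen at T1 and then lost lies anywhere from 0 (all lost by T1) to 94 (all lost after T1). If it is loss by T1, as a calculation for a T1 effect suggests, about 140 reach T1 and the later loss is not stated. These bounds are not an estimate.

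**The case against.** The best defence has four parts.

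**The cost definition is wider than it looks.** App development expenses are added, the resource-use assessment is described as bottom-up, and the questionnaire is not shown, so it may already record medication or interpreters. This stands against any claim that the trial counts consultations and hospital days and nothing else. It does not remove the point: an item recorded by the questionnaire would still not be costed under the Statistical analysis section as written.

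**Leaving interpreters out may be right.** A health-insurance perspective would exclude a cost that insurers need not bear. That is a legitimate choice, and a condensed article may leave the perspective to the full protocol. But the numerator is called actual costs, and nothing in the article ties it to an insurer's view. On any wider view the items belong in.

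**The arms need not differ.** A reader might infer that interpreter cost is the very item on which the arms are expected to differ. The documents do not support this: the translation benefit concerns delivery of information, both arms receive Arabic material, the app is presented as an add-on to routine care, and people in current psychotherapy or psychiatric treatment are excluded. No section predicts a difference in interpreted contacts. This part stands in full.

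**One retrospective questionnaire is a valid design.** If recall reaches back to baseline, T2 covers the whole period. A 16-week QALY also needs EQ-5D-5L at T2, so someone missing T2 lacks a complete effect as well. A drop-out analysis and imputation are planned. All true, and collection at T2 alone is therefore not an error in itself. What remains is that such a participant still supplies T1 effect data to the imputation and no follow-up cost data, and that a single 16-week total, unless asked by period, cannot be set against the T1 effect.

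**Conclusion.** The point holds as a worthwhile, inexpensive improvement to two stated rules of a secondary analysis. It does not touch the primary outcome.

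- The costed services leave out newly started medication and interpreter-assisted contacts. The resulting change in the ICER is zero if the arms use these equally and can go either way if they do not. The documents allow no figure and no sign, so none is given.
- Healthcare use after baseline is observed at T2 alone. Each participant lost between T1 and T2 has 0 of 16 weeks of follow-up cost observed, where 4 of 16 could be had. How many this affects cannot be derived from the 40% dropout allowance.
- Avoided translation cost, as described in the article, largely cancels between the arms and is not measured. The planned economic analysis cannot demonstrate it.

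It would go too far to conclude that the ICER is biased in a known direction or that the T2 schedule is wrong. Both conclusions would need an arm difference or a recall period that the documents do not give.

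**What to change.** 1. **Outcomes, Table 1:** change healthcare resource use from T2 alone to T1 and T2, with recall at each visit reaching back to the previous one.
2. **Statistical analysis:** add medication and interpreter-assisted contacts to the costed items. If the main analysis is to keep a narrower perspective, name that perspective and cost these items in a sensitivity analysis from a wider one. Check that the questionnaire records both, and add them if it does not.
3. **Reporting:** do not present avoided translation cost as an economic result unless it has been costed.

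Cost: a few minutes at the T1 face-to-face interview, which takes place anyway, using a questionnaire that is already to be translated; slightly more burden for participants; and the work of finding unit costs for interpreters and medication. The T1 change has to be made before data collection, because follow-up use not asked at T1 cannot be recovered for those who are later lost.

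### The stated economic result is a plain ICER with a bootstrap interval over 16 weeks; net benefit regression adjusted for baseline utility and baseline costs should be the main analysis instead of an option

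*Protocol article*

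**What the plan says.** The Abstract and the Objectives name the incremental cost-effectiveness ratio as the measure of the app's economic benefit. The Statistical analysis section of the protocol article then sets out the following:

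- Estimator: "the ICER will be calculated as the ratio between the difference of the actual costs and the difference of the averaged treatment effects" between the two groups.
- Effect in the denominator: "indexed by either quality-adjusted life years or primary outcome scores".
- Uncertainty: "Respective confidence intervals will be derived by non-parametric bootstrapping".
- Display: "cost-effectiveness-acceptance curves will be constructed, indicating the probability of an acceptable ICER in relation to willingness to pay for an effect".
- Adjusted analysis: "Alternatively, net benefit regressions [44] can be applied to estimate the respective group specific net benefits", and this "while accounting for potentially confounding variables such as age, sex, and education".

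The ratio and its interval are thus firm commitments, while the regression is something that may be done. Table 1 lists EQ-5D-5L at T0 and at T1/T2, and healthcare resource use at T0 and T2. The caption of Fig. 3 puts the last assessment 16 weeks after baseline. The article does not describe how QALYs are computed, and it gives no utility, QALY or cost figure.

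**The concern.** Cost-effectiveness is a declared aim of the trial, and the result the article commits to is a ratio. Two features make that ratio a weak vehicle.

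First, a follow-up of about four months leaves little room for a QALY difference, so the denominator can lie within one or two standard errors of zero. When resampled denominators fall on both sides of zero, the ratio jumps between large positive and large negative values. A negative ICER can mean cheaper and better or dearer and worse. Percentiles of such a distribution do not form a meaningful interval.

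Second, participants' utility at T0 predicts their later utility and also enters the area under the curve directly. Leaving it out gives up precision exactly where the denominator is fragile. The covariates the article offers as examples are less useful here: randomisation is already stratified by age and sex, and the two baseline measures closest to the economic outcomes are not named.

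At stake is whether the trial can state a cost-effectiveness conclusion with an uncertainty measure that can be read.

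**Working it through.** **Inputs from the protocol article.** Assessments at weeks 0, 4 and 16 (Fig. 3 caption), so the horizon is 16/52 = 0.308 year. Analysable n = 140 at 1:1 allocation, so 70 per arm (Sample size; Allocation and randomization). The baseline figure reproduces: 140/(1 − 0.40) = 233.3, rounded up to 234, or 117 per arm. There is no economic figure to reproduce.

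**Assumptions, not in the documents.** Utility SD 0.20 at each visit; the same correlation r = 0.5 or 0.7 between any two visits; utility gain 0.05 reached at T1 and held to T2; QALYs by the trapezoid rule.

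**1. Weights.** T0: 0.5 × 4/52 = 2/52. T1: 0.5 × (4 + 12)/52 = 8/52. T2: 0.5 × 12/52 = 6/52.

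**2. QALY effect.** 0.05 × (8 + 6)/52 = 0.0135.

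**3. Effect of a chance baseline imbalance.** SE of the T0 utility difference = 0.20 × √(2/70) = 0.0338. The expected shift in the unadjusted QALY difference is 0.0338 × [2/52 + r × 14/52].
- r = 0.5: 0.0338 × 9/52 = 0.0059, or 43% of 0.0135.
- r = 0.7: 0.0338 × 11.8/52 = 0.0077, or 57% of 0.0135.

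**4. Precision of the unadjusted difference.** QALY SD = 0.20 × √[(1 − r)Σw² + r(Σw)²], with Σw² = 104/2704 and (Σw)² = 256/2704. This is 0.052 for r = 0.5 and 0.056 for r = 0.7. Multiplying by √(2/70) gives an SE of 0.0087 and 0.0094. The effect is therefore 1.54 and 1.43 SE from zero, and P(denominator ≤ 0) = Φ(−1.54) = 6.1% and Φ(−1.43) = 7.7%. These are also roughly the bootstrap shares in a trial that observes exactly 0.0135.

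**5. After adjusting for T0 utility.** The squared correlation of T0 utility with the QALY is 0.45 (r = 0.5) and 0.66 (r = 0.7). The SE is multiplied by √(1 − 0.45) = 0.74 or √(1 − 0.66) = 0.58, a cut of 26–42%, to 0.0065 and 0.0055. The effect is then 2.08 and 2.45 SE from zero, and P(denominator ≤ 0) = 1.9% and 0.7%.

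**6. How often the interval would be affected.** A 95% percentile interval is in trouble once more than 2.5% of resampled denominators are at or below zero, that is, when the observed difference is under 1.96 SE. Unadjusted, this happens in Φ(1.96 − 1.54) = 66% to Φ(1.96 − 1.43) = 70% of trials. Adjusted, it happens in Φ(1.96 − 2.45) = 31% to Φ(1.96 − 2.08) = 45%. Adjustment helps, but it does not rescue a ratio interval.

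**7. Sensitivity, P(denominator ≤ 0), r = 0.5–0.7.**

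| Per arm | Utility SD | Gain | Unadjusted | Adjusted |
|---|---|---|---|---|
| 70 | 0.20 | 0.03 | 18–20% | 7–11% |
| 70 | 0.20 | 0.05 | 6–8% | 1–2% |
| 70 | 0.20 | 0.08 | about 1% | under 0.1% |
| 70 | 0.15–0.30 | 0.05 | 2–17% | 0.1–8% |
| 117 | 0.20 | 0.05 | 2–3% | under 0.5% |

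**The case against.** The other side has substantial points.

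- **Baseline utility is not excluded.** The QALY calculation is not described, the covariate list is introduced as examples, and the same section says "Short and medium termed treatment effects will statistically be inferred by using linear mixed effect models accounting for relevant covariates". The full protocol or analysis plan may adjust for T0 utility. A reader might infer that the plan ignores baseline utility, but the article shows only that it does not name it.
- **Imbalance is not bias.** Under randomisation a chance difference at T0 is a source of variance, and the bootstrap carries that variance. This stands. The loss is in precision and in the readability of the ratio interval.
- **The size can be overstated.** A reader might carry the T0 difference undiminished through the whole horizon: 0.0338 × 16/52 = 0.0104, or 77% of the effect. That needs perfect correlation between visits. The direct weight of T0 in the trapezoid is only 2/52, which contributes 0.0013 QALY, about 10%; the rest depends on how strongly utility tracks over time.
- **Acceptability curves are planned.** They remain usable when effects cross zero, and the plan deserves credit for them. As worded, however, they give the probability of an acceptable ICER, which is ambiguous for negative ratios unless computed from net benefit.
- **PDS-5 is the other effect measure.** The article assumes d = 0.5 for it, so the small-denominator argument does not transfer. The wording on the two measures may simply mean that two ICERs will be reported.
- **Development cost.** The article says "The app development expenses will be treated as economically reasonable overhead costs and added accordingly". A reader might infer that this cost is divided among trial participants only, inflating the ICER. No divisor, cost or user number is stated, so the documents do not support that criticism.

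What survives is the ordering: the ratio and its interval are committed to, and the better-behaved adjusted analysis is optional.

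**Conclusion.** The point holds as a choice of analysis that should be improved, not as an error that invalidates the economic evaluation. Under the base assumptions, an unadjusted QALY denominator lies about 1.4–1.5 SE from zero, with 6–8% of estimates at or below zero. An interval for the ratio would then often be uninterpretable. With a utility gain of 0.08 the problem largely disappears; with 0.03 it is clearly worse. The size therefore rests on a utility gain, SD and correlation that the documents do not supply. The structural part does not: a net benefit difference involves no division and is defined whatever the sign of the effect, and the baseline data that would sharpen it are already scheduled.

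**What to change.** Make incremental net monetary benefit on QALYs the main economic analysis. For each participant compute willingness to pay × QALYs − costs, and regress it on study group, T0 EQ-5D utility, T0 healthcare costs, age stratum and sex, over a stated range of willingness-to-pay values. Bootstrap the net benefit difference, and build the planned acceptability curve from it. Report the ICER as a point estimate beside the cost-effectiveness plane, without a ratio interval. Name PDS-5 points as a secondary effect measure.

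The cost is a change of analysis wording. EQ-5D-5L and resource use are already collected at T0, so no extra data or participants are needed. Under the assumptions above, adjusting for T0 utility cuts the standard error of the QALY difference by 26–42%. The gain for net benefit as a whole also depends on cost variance, which cannot be computed from the documents. The downside is that the ratio with its interval is no longer the headline, and readers must interpret results over a range of willingness to pay.
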